### Interventions

Both interventions take place right after the randomization and are carried out by trained healthcare professionals in an empathetic, patient-centered manner and are of similar duration (15–20 min). The attention control group controls for unspecific effects like attention by the healthcare professional or a positive patient-practitioner relationship. The intervention is conducted in addition to clinical routine and is scheduled individually between the healthcare professional and the patient to achieve the best fit in line with the patient’s schedule. Pre-defined as exclusion criteria, concomitant psychotherapy or psychopharmacological treatments are prohibited. Also as part of the clinical routine, all patients receive prescriptions for medications against nausea/vomiting and diarrhea.

#### Nocebo-education group

The nocebo-education is a manualized information session with the objective of illustrating the nocebo effect in a comprehensive way using patient-oriented language and practical examples [18]. It was developed as part of an experimental pilot-study by the research team of the PI of this study (YN) and has been adapted according to patient feedback. The intervention includes the following five steps: (1) The healthcare professional asks the patient about their personal experiences with side effects of medications or other treatments. (2) A case example of a nocebo response in the clinical context is introduced and discussed (adapted from [29]). (3) A standardized leaflet about the nocebo effect is handed out (see Table 2) and discussed. Patients are invited to talk about their own thoughts and potential prior experiences with nocebo responses. (4) Lastly, patients are encouraged to apply the obtained information to their imminent chemotherapeutic experience. The manual accounts for potential deviations of patients’ experiences and recall abilities (e.g. if the patient cannot recall any individual nocebo responses, the health professional may use a personal example).

**Table 2 Tab2:** Brief discussion points from the leaflet of the nocebo-education

Information sheet about side effects	
A) The occurrence of side effects has two essential causes: • Pharmacological (substance-dependent) causes which activate biochemical reactions in the body • Psychological (non-substance dependent) causes which mainly include prior experiences and expectations of patient and relevant aspects of the therapeutic context (called the nocebo effect)	
B) Nocebo effects: education and exemplification • Nocebo effects are no illusions, but real and biologically measurable effects. • Prior negative experiences with adverse effects of drugs or even just reading about them in a medication leaflet can increase negative expectations of developing side effects. This might in turn lead to an increased actual occurrence of side effects.	
C) Case example of nocebo effects: • *“For my next checkup, I was to receive a contrast agent. I was anxious, knowing that my body reacts strongly to that kind of thing. The nurse hooked me up to the IV, through which the contrast agent would enter my body. She told me that the contrast agent would make me feel hot and that there might be a burning sensation. She then left me alone. The minute she left the room, I felt the heat washing over me, it streamed through my body and it burned. I knew this checkup was going to be awful. I felt extremely frightened. After a few minutes the doctor entered the room and she told me: Ok, let‘s inject the contrast agent, shall we?*” *(adapted from* [29]*)*	
D) Empathetic encouragement to explore own examples of nocebo effects. Gain reassurance that possible adverse effects of chemotherapy may be affected by own expectations.	

#### Attention control group

A face valid topic of matching relevance to the research topic of this trial is discussed with the patients in the attention control group in a similarly manualized manner. Based on the Functional Assessment of Cancer Therapy general scale (FACT-G; [30]), the healthcare professional makes inquiries about the quality-of-life subthemes physical well-being, emotional well-being and functional well-being using a semi-structured interview format. The two themes beliefs and spirituality, and relationship to practitioners which are not part of the scale are additionally addressed. Twenty questions are asked in total. The healthcare professional or the patient may address issues in further depth. Some items are rephrased to achieve a balance of negatively and positively phrased items (e.g. “I am worried that my condition will worsen” is rephrased as “I am optimistic about the future”). Answers are noted on the questionnaire. Answers to the interview are not part of the research questions and are hence not analyzed.

### Data collection and confidentiality

Self-report data is collected at before and after the intervention (T1-pre and T1-post) by the healthcare practitioner. Further self-report data at 10 days and 12 weeks follow-up is collected via mail. Medical characteristics are assessed using medical records. Clinician-rated data are collected at every chemotherapy cycle. All data in paper form will be stored at the UMC Hamburg-Eppendorf in rooms inaccessible to non-research staff. Since we conduct repeated measurements, identifying information of the patient is substituted by a code. Patients’ personal information (name, phone number, address) are securely stored separately from data which are outlined under “measures”.

### Measures

#### Primary outcomes

The mean group difference in number and intensity of patient-reported side effects at 10 days and 12 weeks after the initial chemotherapy session are defined as primary outcomes. Based on the Generic Assessment of Side Effects (GASE) [31], we chose four side effects specific to the chemotherapy, i.e., nausea, vomiting, diarrhea, and fatigue [32, 33]. Three unspecific symptoms, i.e., headache, shortness of breath, and rash, were defined as side effects that were very unlikely to occur in pharmacodynamic relation to the chemotherapy. They were chosen as a result of discussions among the research staff oncologists. A global item assesses the overall intensity of side effects in the last 7 days. The original GASE ranged from 0 to 3; to optimize outcome sensitivity in this exploratory trial, we increased the item range from 0 (*not at all*) to 10 (*very much*). Numbers of side effects are computed by adding up the number of present symptoms (≥ 1).

#### Secondary outcomes

Coping with side effects, the tendency to misattribute symptoms, compliance intention, attitude towards the chemotherapy, co-medication to treat side effects, and clinician-rated severity of toxicity measured at 10 days and 12 weeks after the initial chemotherapy session are examined as secondary outcomes. Coping with side effects is assessed as part of the GASE (GASE-Coping; varied after [34]). For each side effect, patients are asked to indicate how well they felt able to cope with the symptom (0 ‘*not at all*’ to 10 ‘*very much*’). Accordingly, the tendency to attribute symptoms (“To which degree do you attribute [symptom] to the chemotherapy?”) is assessed for each side effect on the same scale. The tendency to misattribute is computed as the mean attribution tendency of unspecific symptoms to the chemotherapy. Compliance intention to chemotherapy is assessed with two items (“How sure are you that you will complete your chemotherapy cycle?” from 0 “*not at all*” to 10 “*very much*”; “How high is the probability that you will discontinue your chemotherapy?” from 0 to 100%). Attitude towards the chemotherapy is measured using one item (“How would you describe your attitude towards the chemotherapy”) which ranges from 0 (*very negative*) to 10 (*very positive*). Co-medication to treat side effects is assessed with a yes/no question. The clinician-rated severity of toxicity is assessed using the Common Toxicity Criteria (CTC) Version 4.03 at every cycle. The CTC provides standardized definitions of adverse events ranging from grade 1 to grade 5 with each grade reflecting a distinct description of the adverse events severity [35].

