^a^The eligibility screening takes place in two steps. In the first step, medical eligibility criteria are checked, whereas in the second step, all further criteria are assessed as part of the health professional-patient communication right before the signing of the informed consent

^b^Assessed symptoms include fatigue, nausea, diarrhea, vomiting, headache, shortness of breath, and rash

^c^Severity of toxicity is assessed by the clinician at every cycle

^d^Knowledge about the nocebo effect is only assesses in the nocebo education group

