#### Manipulation check, evaluation of the nocebo-education, process variables

Comprehension of the nocebo effect information is reviewed by asking patients in the nocebo group to describe the nocebo effect. Perceived relevance of the nocebo-education and the control intervention is assessed at T1-post. Expected efficacy of chemotherapy includes four items that assess to which degree the patient anticipates the treatment will 1) help them recover, 2) shrink the tumor, 3) improve their quality-of-life and 4) prolong their life. Each item ranges from 0 (*not at all*) to 10 (*very much*). Progression of cancer is assessed from medical records during the study period.

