### Statistical methods

All outcome analyses will be conducted for the intention-to-treat sample. Missing values will be imputed using the expectation-maximization algorithm. We will conduct ANCOVA for the primary outcomes number and intensity of side effects, and for the secondary outcomes coping with side effects, tendency to misattribute symptoms, compliance intention, attitude towards chemotherapy, and medical toxicity at both time points (10 days and 12 weeks) with adjustments for the stratum distress and for cancer staging. Logistic regression will be conducted for the secondary outcome co-medication to treat side effects with the same set of covariates. The T1-pre to T1-post changes in expected side effects and expected coping with side effects will be examined as mediators of the effect of group on the outcomes. Exploratory analyses will be conducted to compare the expected efficacy of the chemotherapy between groups using independent t-tests.

Moderate analyses will be carried out by including the group x information coping style interaction in the ANCOVA. Sensitivity analyses will be conducted under exclusion of (1) patients of the nocebo-education group who either indicated to not have heard about the nocebo effect or who gave a wrong description and (2) patients with tumor progression.

No interim analyses will be conducted.

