## Discussion

This is the first study to evaluate whether a nocebo-education can have beneficial effects considering side effects of the chemotherapy when compared to an attention control group. Up to now, no study has evaluated whether informing patients about the nocebo effect would be useful to optimize expectations and decrease side effect load in clinical practice. If efficacious, this trial would contribute to solving the ethical dilemma posed by the necessity and importance of informing the patients about the treatment on the one side and the potential negative effects of the information on the development of side effects on the other. Our objective was to create a nocebo-information session which is short, patient-oriented, and feasible in regard to implementation into clinical routine. Also, since the nocebo-education can be provided additional to the practitioner’s information, no further changes to the clinical practice are necessary.

The following limitations should be noted: As the first exploratory trial to test hypothesized effects of a nocebo-education, the sample size in this study is rather small. Also, no specific power calculation was possible since the effects of a nocebo-education on side effects are unknown. Given the link between side effect expectations and side effects, we based our power calculations on the effects of a nocebo-education on side effect expectations. Nonetheless, the use of a proxy outcome for the sample size calculation constitutes a limitation. Due to the nature of the study, blinding of patients and healthcare professional was not possible. Whereas the healthcare professional is the assessor at T1-pre and T1-post, outcome assessments at 10 days and 12 weeks after the initial chemotherapy are conducted via mail to lessen potential biases through the assessor. Since our patient population is expected to be highly burdened, we aim to keep the additional effort which may arise through questionnaire completion to a minimum. Hence, except for our primary outcomes, we use several one-item or two-item questionnaires which have not been previously validated. Lastly, our primary outcome is based on patient self-report. If this trial shows beneficial effects of the nocebo-education, further studies including physiological measures or clinician-rated measures as primary outcomes would be valuable.

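### The stated toxicity analysis uses neither the baseline rating nor the other cycle ratings of the only outcome explicitly rated by a clinician

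*Protocol article*

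**What the plan says.** Three places in the protocol article tie clinician-rated toxicity to treatment cycles. The footnote to Table 1 says "Severity of toxicity is assessed by the clinician at every cycle", Data collection and confidentiality says "Clinician-rated data are collected at every chemotherapy cycle", and Secondary outcomes says "The clinician-rated severity of toxicity is assessed using the Common Toxicity Criteria (CTC) Version 4.03 at every cycle". Table 1 also ticks the CTC at T1-pre, T2 and T3.

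The outcome is defined more narrowly: "clinician-rated severity of toxicity measured at 10 days and 12 weeks after the initial chemotherapy session are examined as secondary outcomes". Statistical methods follows that definition, with ANCOVA for "medical toxicity at both time points (10 days and 12 weeks) with adjustments for the stratum distress and for cancer staging". The T1-pre CTC rating is not among the covariates, and no analysis of the other cycle ratings is described.

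On the remaining outcomes, the Discussion states: "Lastly, our primary outcome is based on patient self-report". Co-medication, the one binary secondary outcome, rests on a simple question ("Co-medication to treat side effects is assessed with a yes/no question") whose respondent is not named. Progression does come from records ("Progression of cancer is assessed from medical records during the study period"), but it defines a sensitivity exclusion and is not a primary or secondary outcome.

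**The concern.** Patients know which session they had, and those in the education arm are told that expectation can produce side effects. A lower patient-rated score in that arm could therefore mean fewer symptoms or a changed readiness to report or attribute them. A rating made by someone else helps to tell these apart, and among the primary and secondary outcomes only the CTC is explicitly of that kind. The Discussion itself lists self-report as a limitation and hopes for clinician-rated measures in later studies.

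The trial already collects such a measure repeatedly and before treatment effects set in, yet the stated analysis takes two time points without baseline adjustment. At stake is the precision of a supporting comparison that would help readers interpret the primary result. The primary result itself is not at stake.

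**Working it through.** **1. The plan's own figure.** Sample size calculation uses d = 0.60, two-sided alpha 0.05, power 80% and 10% dropout. A two-sample t-test (noncentral t) needs 44.59, so 45 per group, and 90 / 0.9 = 100. Both stated figures reproduce. They concern the primary outcome and do not depend on how toxicity is analysed.

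**2. Collected against analysed.**

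| CTC rating | Collected | In the stated analysis |
|---|---|---|
| T1-pre | yes (Table 1) | no; covariates are distress and staging |
| 10 days, 12 weeks | yes (Table 1) | yes, one ANCOVA each |
| Other cycles | yes (three statements) | none described |

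**3. Value of the other ratings.** The article gives neither the number of ratings k by week 12 nor the within-patient correlation ρ. I assume k = 4–6, ρ = 0.4–0.6, equal correlation between all pairs of ratings and a constant treatment effect. Relative to one rating, the variance of a patient's mean is

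V(k) = (1 + (k − 1)ρ) / k.

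| k | ρ = 0.4 | ρ = 0.6 |
|---|---|---|
| 1 | 1.00 | 1.00 |
| 2 | 0.70 | 0.80 |
| 4 | 0.55 | 0.70 |
| 5 | 0.52 | 0.68 |
| 6 | 0.50 | 0.67 |

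- Against one rating: 1 − 0.70 = 30% to 1 − 0.50 = 50% lower variance. This is worth 1/0.70 = 1.43 to 1/0.50 = 2.00 times the patients.
- Against the mean of two: the smallest gain is 1 − 0.70/0.80 = 12.5% (k = 4, ρ = 0.6) and the largest is 1 − 0.50/0.70 = 28.6% (k = 6, ρ = 0.4). This is worth 0.80/0.70 = 1.14 to 0.70/0.50 = 1.40 times the patients.

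**4. The same in power.** With 45 per group and standardised effect d/√V(k):

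| d | ρ | k = 1 | k = 2 | k = 4 | k = 6 |
|---|---|---|---|---|---|
| 0.60 | 0.3 | 80.4% | 93.7% | 98.3% | 99.2% |
| 0.60 | 0.5 | 80.4% | 90.2% | 94.5% | 95.8% |
| 0.60 | 0.9 | 80.4% | 82.3% | 83.3% | 83.6% |
| 0.40 | 0.5 | 46.7% | 58.2% | 66.0% | 69.0% |

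At d = 0.60, going from two ratings to 4–6 adds about 1 to 6 points across ρ = 0.3–0.9. Part of the reason is that power is already near its ceiling. At d = 0.40 and ρ = 0.5 it adds 66.0 − 58.2 = 7.8 to 69.0 − 58.2 = 10.8 points. Neither effect size is a documented toxicity effect: 0.60 comes from side effect expectations in the pilot study, and 0.40 is my assumption.

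**5. Value of the baseline rating.** Adjusting for a baseline with correlation r to the outcome multiplies the residual variance by about 1 − r². The article does not give r. At r = 0.4 the factor would be 1 − 0.16 = 0.84. Patients are chemotherapy-naive at enrolment, so T1-pre grades may vary little and r may well be lower. This gain does not simply add to that in step 3, because baseline adjustment also removes part of the between-patient variance.

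**The case against.** The strongest reply is that nothing here is an error. Toxicity is one of six secondary outcomes in a trial that calls itself exploratory. Analysing it at the primary outcome's two time points keeps it directly comparable with the patient ratings and avoids a summary that depends on how many cycles a patient received. Regimens and treatment settings are mixed, so that number may differ between patients. An average over cycles is also a different estimand from a day-10 or week-12 effect, and would dilute an early effect that fades. All of this stands, and it is why the two ANCOVAs should stay as the stated analysis.

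Four stronger readings are tempting, and the article does not support them:

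- *The other ratings are discarded.* No use is described, but nothing says they go unused, and the full protocol and analysis plan are not shown.
- *The 10-day value must be borrowed from another visit.* Table 1 ticks the CTC at T2 and T3. Only the self-report data are said to come by mail, and cycle length is not given.
- *The lack of a rule linking cycles to the two time points is a defect.* Such rules are commonly left to the full documents.
- *The plan gives up 30–50% in variance.* That range compares with a single rating. It fits each ANCOVA taken alone, but then the estimands differ. Against both time points averaged, the range is 12–29%.

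It is also fair to say that CTC grades for symptoms such as nausea or fatigue depend partly on what patients tell the clinician, so the CTC is not fully independent of reporting. That limits how much any toxicity analysis can settle. It does not remove the case for using the ratings.

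**Conclusion.** The point holds as an improvement to a legitimate analysis, not as a contradiction or an error. The article states that the CTC is rated at baseline and at every cycle, and it states an analysis that uses two post-treatment time points without the baseline. For the only primary or secondary outcome explicitly rated by a clinician, in an unblinded trial with self-reported primary outcomes, that leaves available information out of the stated analysis.

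The size is illustrative: about 12–29% lower variance than the mean of two ratings, or 30–50% lower than one. It rests on assumed values of 4–6 ratings and a correlation of 0.4–0.6, with equal correlations and a constant effect. The gain from baseline adjustment cannot be sized from the article. The stated sample size, alpha and primary analysis are unaffected.

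**What to change.** In Statistical methods:

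1. Add T1-pre CTC as a covariate, next to distress and staging, in the two planned toxicity ANCOVAs. Keep these as the stated secondary analysis.
2. Add a supportive repeated-measures model of all CTC ratings from the first cycle to week 12, with group, time, distress, staging and T1-pre CTC, allowing for unequal numbers of ratings per patient. The T1-pre rating enters as a covariate only, not also as a response.
3. Label the second analysis as supportive and describe its estimate as an average over time.

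The data are already collected, so the cost is analysis wording and a little more work. The downside is that the supportive estimate would understate an early effect that fades, so it should be read beside the two time-point results and not in their place.

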## Background

Gastrointestinal tumors, including cancer of the esophagus, stomach, colon, rectum, anus, pancreas, gallbladder and bile duct, constitute the largest group of cancer for men, and the second largest group of cancer for women [1]. Further, they are characterized by high mortality rates [1]. One of the treatment options for gastrointestinal tumors is chemotherapy, which can be indicated in the neoadjuvant, adjuvant or palliative setting [2]. Due to the high toxicity of the chemotherapy, cancer patients are commonly burdened by side effects of varying severity which may impair quality-of-life [3, 4]. Furthermore, side effects have substantial weight in the individual decision process of whether or not to proceed with chemotherapy and were shown to be one of the three major predictors of treatment discontinuation in the palliative setting [5, 6]. Strikingly, side effects are not fully defined by the pharmacodynamics of a given drug, but can also be caused by psychological factors. These so-called nocebo effects are best known as the counterparts of placebo effects [7]. The nocebo effect can depend on a variety of factors, e.g. the patient-practitioner relationship, a patient’s treatment expectations, or prior learning experiences [8]. Nocebo-driven side effects can occur as unspecific side effects, i.e. symptoms not explainable by the drug, or may also exacerbate specific side effects [9]. Studies which investigated adverse events after placebo intake [10, 11], as well as studies which used verbal suggestions to manipulate treatment expectations prior to medication intake, demonstrated the existence of nocebo effects [12–14].

One of the main underlying mechanisms for the development of nocebo effects is expectations. These are formed based on prior experiences (either specific to the treatment or in general, to medical procedures) [15], social learning [16], and the information received about the treatment [17].

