### Study sample

Patients with newly diagnosed cancer of the gastrointestinal tract, including the esophagus, stomach, colon, rectum, anus, pancreas, gallbladder and bile duct who are indicated for chemotherapy are eligible for this study. Chemotherapy can be given in the adjuvant, neoadjuvant, or first-line palliative setting, and is administered as a mono chemotherapy or combination-chemotherapy, with or without vascular endothelial growth factor (VEGF)-antibody. To enroll, patients must be at least 18 years old, have no difficulties understanding German, and be able to give informed consent. Exclusion criteria include the following: any chemotherapy before trial inclusion, limited capability of self-care (Eastern Co-operative Oncology Group (ECOG) ≥ 3 [26]), severe comorbid psychological disorder (schizophrenia, substance abuse, severe depression or severe anxiety disorder), concurrent psychotherapeutic or psychopharmacological treatments, life-threatening comorbid medical condition, diagnosis of chronic skin disease, dyspnea, or chronic lung diseases due to its interference with chemotherapy side effects, indication for epidermal growth factor receptor (EGFR)-antibody treatment since it may cause acne-like rash. Since prior research has found that the link between negative treatment expectations and side effects was more pronounced among patients who had chemotherapy experience [19], we excluded patients with prior chemotherapy experience, including having received the first dose before enrolment, to achieve an increased homogeneity of the sample.

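### At 12 weeks the compliance-intention items have no valid answer for patients whose chemotherapy has ended, yet they enter the intention-to-treat ANCOVA under a blanket imputation rule

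*Protocol article*

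**What the plan says.** **Items.** In the Protocol article, Secondary outcomes, compliance intention consists of two items: "How sure are you that you will complete your chemotherapy cycle" (0 to 10) and "How high is the probability that you will discontinue your chemotherapy" (0 to 100%). The secondary outcomes, compliance intention among them, are "measured at 10 days and 12 weeks after the initial chemotherapy session are examined as secondary outcomes". Table 1 schedules compliance intention at T1-pre, T1-post, T2 and T3.

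**Timing.** Under Study design, T2 and T3 are counted from the first chemotherapy. T3 is not tied to a point in the treatment course.

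**Analysis.** Under Statistical methods, compliance intention is among the outcomes analysed by ANCOVA "at both time points (10 days and 12 weeks) with adjustments for the stratum distress and for cancer staging". The same section states: "All outcome analyses will be conducted for the intention-to-treat sample". It continues: "Missing values will be imputed using the expectation-maximization algorithm". No exception is given for items that no longer apply.

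**Population.** Under Study sample: "Chemotherapy can be given in the adjuvant, neoadjuvant, or first-line palliative setting". The Background says that side effects "were shown to be one of the three major predictors of treatment discontinuation in the palliative setting".

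**The concern.** Both items ask what will happen to the chemotherapy. Once it has ended, there is no future completion or discontinuation to rate. The word cycle in the first item could mean one cycle or the whole course, but neither reading gives an answer after treatment is over.

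Some patients may well be in that position at T3. The sample mixes three treatment settings, the Background names discontinuation as a known consequence of side effects, and tumour progression is followed during the study. The plan nevertheless analyses the score in everyone and imputes whatever is missing.

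What is at stake is the meaning of the 12-week comparison. A patient who stopped early has had the very event that a compliance measure is meant to anticipate. That patient may enter with an imputed intention to continue, or with an answer that is not an intention at all.

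**Working it through.** **The plan's own figure.** For d = 0.60, two-sided alpha 0.05 and 80% power, a two-sample t-test needs 44.6, so 45 per group. Allowing for 10% dropout, 90/0.9 = 100. The stated size is reproduced and is not in dispute. It is used below as 50 randomised per arm.

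**What the rules do with an off-treatment patient at T3**

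| Patient's response | Treatment under the stated rules | Consequence |
|---|---|---|
| Leaves the items blank | Missing, so filled by EM | Receives an intention modelled on patients who answered |
| Answers anyway (e.g. stopped: 0 and 100%; completed: 10 and 0%) | Observed, not imputed | A fact is averaged with other patients' intentions |

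The protocol does not say which of the two will occur.

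**Illustration of the blank case.** None of these inputs is in the protocol; all are assumptions. Take an on-treatment mean of 8.5 (SD 1.5) in both arms, and score a stopper 0 by convention. If stoppers counted as 0, the difference between arms would be 8.5 × (control share − education share):

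- 10% vs 5%: 8.5 × 0.05 = 0.43
- 20% vs 10%: 8.5 × 0.10 = 0.85
- 30% vs 15%: 8.5 × 0.15 = 1.28
- 40% vs 20%: 8.5 × 0.20 = 1.70

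A simulation of 4,000 trials with 50 per arm imputed blanks by regression on the T2 score (correlation 0.5) and group. It gave 0.83, 1.29 and 1.69 for the last three scenarios before imputation, and about 0.0 after. The zero is built in: the on-treatment means were set equal, and blanks did not depend on the T2 score. It shows what can happen, not what will.

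**If EM uses the patient's own earlier answers.** Under the same assumptions, a stopper whose T2 score lay k SDs below average is filled with 8.5 − 0.5 × 1.5 × k. For k = 2 this is 8.5 − 1.5 = 7.0. At 20% vs 10% stopping, the imputed scores would then carry (8.5 − 7.0) × 0.10 = 0.15 points instead of 0.85. The masking is partial, but still large.

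**The answered case.** A completer who writes 10 differs from the assumed on-treatment mean by 1.5. Each 10-percentage-point difference between arms in completion therefore shifts the comparison by 0.15 points, without any difference in intention.

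**Power of a comparison of early stopping.** Normal approximation, 50 per arm: power = Φ(|p1 − p2| / √[(p1(1−p1) + p2(1−p2))/50] − 1.96).

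- 10% vs 5%: 0.05/√(0.1375/50) = 0.95; power 16%
- 20% vs 10%: 0.10/√(0.25/50) = 1.41; power 29%
- 30% vs 15%: 0.15/√(0.3375/50) = 1.83; power 45%

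With 45 per arm the same formula gives about 15%, 27% and 41%.

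**The case against.** The strongest reply is that the protocol imputes missing values and nowhere says that off-treatment patients leave these items blank. A patient who stopped can write 0 and 100%, and those values would be kept. This stands: the imputation harm is conditional. A reader might infer that every patient who discontinues is given a favourable score, so that any effect on discontinuation disappears. The text does not support that. It fixes neither the blanks nor the contents of the EM model, which may include the patient's own T1 and T2 answers.

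Second, no chemotherapy duration or stopping rate is given. Toxicity is rated at every cycle and also scheduled at T3, which is compatible with many patients still being on treatment then. This also stands: the affected share could be small.

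Third, the outcome is intention, not adherence, so 0 is not the true score of a stopper. Agreed; 0 above is a scoring convention. But this confirms that an intention score is undefined for that patient.

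Fourth, handling of not-applicable answers may sit in a fuller document that is not shown. That would excuse silence on skip instructions. The point rests instead on rules the article does state: these items, at T3, in the full sample, with a general imputation rule.

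Finally, an obvious repair, running the ANCOVA only in patients still on chemotherapy, would select on an event after randomisation. That objection is right, and the fix below avoids it.

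**Conclusion.** The point holds in a limited form. As written, the 12-week compliance-intention comparison has no clear meaning for patients whose chemotherapy has ended, whether they answer or not. If they leave the items blank, imputation can hide early discontinuation.

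The size is unknown because the share off treatment is not stated. The 0.4 to 1.7 points above rest on assumed stopping rates of 10/5% to 40/20%, an on-treatment mean of 8.5 and a score of 0 for stoppers. They mark the order of magnitude if stoppers leave the items blank and are not a forecast.

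The effect is confined to one secondary outcome at one of two time points in an exploratory trial. The primary outcomes, the sample size and the 10-day planned comparison are not called into question. The change is still worth making, because it is cheap and the present T3 result could not be interpreted.

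**What to change.** 1. Record treatment status at T3 (ongoing, completed as planned, stopped early) from the medical records, which the study already uses for regimen and progression. State in advance how stopping after progression, and death before T3, are classified.
2. Make early stopping versus ongoing or completed the T3 comparison, in all randomised patients, by logistic regression with the covariates already planned.
3. Exempt compliance-intention items that no longer apply from EM imputation.
4. Report T3 intention among patients still on chemotherapy descriptively only, because that subset is formed after randomisation.
5. Keep the T2 ANCOVA in the intention-to-treat sample and add the T1-pre compliance score. It is collected according to Table 1 but is not among the stated covariates. This is a gain in precision, separate from the problem above: at an assumed correlation of 0.5 it removes 0.5² = 25% of the residual variance.

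**Cost.** One status field and a few lines of analysis text. Status can be retrieved for patients who have already passed T3, but for those from cooperating practices it may have to be requested there. The T3 intention score is no longer formally tested. The early-stopping comparison has low power, about 16% to 45% in the three scenarios worked above. At 10% vs 5% only 5 + 2.5 = 7.5 events are expected, so a penalised likelihood or fewer covariates may be needed. The result should be read as an estimate with its confidence interval.
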